### **8.0 SAFETY ANALYSIS**

#### **8.1 Ancillary Component**

Safety analyses for the Ancillary Component will be generated for the Safety Population and the Safety Population with a baseline COWS of 0-3.

##### **8.1.1 Safety Events**

An overall summary of safety events by site will be provided. This table will include the frequency and percent of participants experiencing a COWS score increase of 5 or greater within 4 hours of injection, transitioning to moderate withdrawal (COWS score 13 to 24, inclusive) within 4 hours of injection, experiencing a precipitated withdrawal (captured 4 hours post-injection), experiencing at

least one AE, and experiencing at least one SAE. The total number of AEs and SAEs will also be provided in this table.

### **8.1.2 COWS Scores Post-injection**

A spaghetti plot of change in COWS score from baseline at each of the post-baseline measurements will be provided by whether the participant was positive for fentanyl at baseline, taken from the UDS eCRF. Participants experiencing a 5 or greater increase in the COWS score will be highlighted in the plot.

### **8.1.3 Adverse Events**

Treatment emergent adverse events (AEs) will be summarized by presenting number of participants experiencing AEs, the maximum severity for participants, the number of AEs, and the severity and relatedness by treatment arm. AE will also be summarized by system organ class and preferred term using MedDRA® dictionary version 25.0 or higher. Adverse events will be presented as the number and proportion of participants experiencing at least one incidence of each event and will be presented overall and by treatment arm.

Similar tables may be created for SAEs. For SAEs, the classification of SAE rather than severity will be summarized.

A listing of all AEs experienced in the Ancillary component will be presented. This listing will include enrollment date, date of XR-BUP injection, onset date of the AE, description of the AE, severity of the AE, relatedness to study drug (as 'Yes' or 'No'), AE outcome, resolution date (if applicable), and what the AE was associated with to be classified as an SAE. SAEs will be included in this table and will be highlighted in grey. The System Organ Class (SOC) and preferred term (PT) coded using a MedDRA dictionary version of 25.0 or higher will be included in this listing.

### **8.1.4 Injection Site Assessments**

A summary table of injection site assessments will be provided by site. Injection site assessments are expected at the Day 7 follow-up visit. This will include the number and percent of injection site assessments, number and percent experiencing a delayed reaction since the injection, number and percent experiencing at least one symptom, the number of each symptom experienced and percent out of all symptoms experienced.

### **8.1.5 Post-injection Medications**

Post-injection medications provided to participants will be listed. This will include the time of injection, the medication given, the administration time, the dose (in mg), and the route (for example oral, sublingual, or intravenous).

### **8.1.6 Suicidal Ideation**

A summary table will be provided by site of answers to the question 'Over the last two weeks, how often have you been bothered by thoughts that you would be better off dead, or of hurting yourself in some way?' asked on the Patient Health Questionnaire (PHQ-9) collected on the Health Status (HST) eCRF at baseline. Possible responses to this question are 'Not at all', 'Several days', 'More than half the days', and 'Nearly every day'.

### **8.1.7 Opioid Overdose Events**

A summary table will be provided with the number of non-fatal opioid overdoses (OD) by site and by visit (baseline and Day 7 follow-up) as captured on the ODE eCRF. At the baseline visit, participants are asked about overdoses in the past 30 days. At the Day 7 follow-up visit, participants are asked about overdoses in the past 7 days following their XR-BUP injection. The number of ODs where NARCAN (naloxone) was used to reverse overdose, resulted in treatment

at an ED, and resulted in being admitted to the hospital will also be summarized, among the 1 to 5 most serious opioid overdoses reported by the participant at each visit. The number of participants with at least one opioid overdose and the number of opioid overdoses per participant (including participants experiencing no opioid overdoses) will also be summarized.

### 8.1.8 Death

A listing of all deaths will be presented and will include all variables in the AE listing described in Section 8.1.3.

## 8.2 RCT Component

Safety analyses will be performed for the **safety population**. Results will be summarized by treatment arm and overall.

### 8.2.1 Adverse Events

Treatment emergent adverse events (AEs) will be summarized by presenting number of participants experiencing AEs, the maximum severity for participants, the number of AEs, and the severity and relatedness by treatment arm. AE will also be summarized by system organ class and preferred term using MedDRA® dictionary version 25.0 or higher. Adverse events will be presented as the number and proportion of participants experiencing at least one incidence of each event and will be presented overall and by treatment arm.

Similar tables will be created for SAEs. For SAEs, the classification of SAE rather than severity will be summarized.

A listing of all AEs will be presented. This listing will include enrollment date, date of first dose injection, onset date of the AE, resolution date (if applicable), description of the AE, severity of the AE, relatedness to study drug (as 'Yes' or 'No'), AE outcome, and what the AE was associated with to be classified as an SAE. SAEs will be included in this table and will be highlighted in grey. The MedDRA System Organ Class (SOC) and preferred term (PT) using version of 25.0 or higher will be included.

### 8.2.2 Injection Site Assessments

A summary table of injection site assessments will be provided. Injection site assessments are expected at the Day 7 follow-up visit. This will include the number of injection site assessments, number and percent experiencing a delayed reaction since the injection, number and percent experiencing at each symptom, the number of each symptom experienced, and percent out of all symptoms experienced.

A listing of injection site reactions will be generated that includes the date of the assessment, the symptoms reported (and severity if applicable), and verbatim terms for any abnormalities categorized as 'other'.

### 8.2.3 Suicidal Ideation

A summary table will be provided by site of answers to the question 'Over the last two weeks, how often have you been bothered by thoughts that you would be better off dead, or of hurting yourself in some way?' asked on the Patient Health Questionnaire (PHQ-9) collected on the Health Status (HST) eCRF at baseline. Possible responses to this question are 'Not at all', 'Several days', 'More than half the days', and 'Nearly every day'.

A listing of suicidal ideation will be generated that includes the date of the assessment and the response to the question above.

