### 8.9.4 Adverse Events (AEs) and Serious Adverse Events (SAEs)

Adverse events will be captured and reported through the Adverse Event (AE) reporting mechanisms described in Section 18. Events including withdrawal (except for precipitated withdrawal), injection site reactions, assessments for suicide risk, overdose and vital signs do not need to be reported as Adverse Events and will be captured on specific study forms. If any of these events meet the definition of a SAE described in Section 18, then they would be reported on the AE/SAE forms set.

The reporting period for AEs and SAEs for the RCT starts at XR-BUP administration and ends at the last study visit, day 30 after enrollment.

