#### **14.24 Adverse Events (AEs)**

The Site PI or Co-I will review or provide consultation for each AE/SAE, as needed. These reviews will include an assessment of the possible relatedness of the event to the study intervention or other study procedures. The Site PI or Co-I will also provide advice for decisions to exclude, refer, or withdraw participants as required. In addition, NIDA will assign a Medical Monitor to this protocol to independently review the safety data, present it to the DSMB for periodic review, and provide PIs a Safety Letter when necessary. The Medical Monitor will determine which safety events require expedited reporting to NIDA, the DSMB, pharmaceutical, and regulatory authorities. This will include events that are serious, related, and unexpected. The study staff will be trained to monitor for and report AEs and SAEs. Additionally, as applicable, sites will submit reporting of AEs/SAEs according to IRB requirements. Each of the sites has established practices for managing medical and psychiatric emergencies, and the study staff will continue to utilize these procedures. Treatment providers at each site will be responsible for monitoring participants for possible clinical deterioration or other problems, and for implementing appropriate courses of action.

Safety for this study will be monitored through specific study assessments and medical record abstraction in addition to more standard AE/SAE reporting.

Depression/Suicidality: The PHQ-9 will be assessed at baseline and at 7 and 30 days post enrollment for the RCT. If the answer to question the question, “Over the past two weeks, how often have you been bothered by thoughts that you would be better off dead or of hurting yourself in some way?” is greater than “Not at all,” research staff will activate local procedures to ensure participant safety. The policies and procedures at that ED regarding assessment by a qualified clinician before leaving will be specified in the site clinical SOP.

Injection Site Examination: Participants will be asked to immediately report any unanticipated injection site reactions to study staff for evaluation, monitoring, and possible referral, as needed. Injection site reactions will be documented on the Injection Site Abnormality form.

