## Site's Role in Eliciting and Reporting Adverse Events

Appropriately qualified and trained personnel will elicit participant reporting of AEs and SAEs at each study visit designated to collect AEs. Adverse events (medical and/or psychiatric) assessment will initiate with participant consent and follow-up of reported AEs will continue through 30 days post last study visit for RCT and through 7 days for ancillary components. Study personnel will obtain as much information as possible about the reported AE/SAE to complete the AE/SAE forms and will consult as warranted.

Standard reporting, within 7 days of the site becoming aware of the event, is required for reportable AEs. Expedited reporting (within 24 hours of their occurrence and/or site's knowledge of the event) is required for reportable SAEs (including death and life-threatening events). Local sites are responsible for reporting SAEs to the IRB of record, per the IRB of record's guidelines.

Sites are required to enter reportable AEs and SAEs in the Advantage eClinical system. The AE form is used to capture reportable AEs and SAEs (as defined in the protocol). Additional information may need to be gathered to evaluate SAEs and to complete the appropriate CRFs and the summary. This process may include obtaining hospital discharge reports, medical records, autopsy records or any other type records or information necessary to provide a complete and clear picture of the serious event and events preceding and following the event. If the SAE is not resolved or stable at the time of the initial report or if new information becomes available after the initial report, follow-up information must be submitted as soon as possible.

Reportable adverse events will be followed until resolution, stabilization or study end. Any serious adverse reactions will be followed until resolution or stabilization even beyond the end of the study.

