#### **3.2.1.3 Safety Population**

The safety population includes all participants who completed the informed consent for the RCT component during the screening visit and received treatment. Safety analyses will be performed according to the participant's randomized treatment arm.

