#### **8.2.4 Precipitated Withdrawals**

A table summarizing the number of participants experiencing a precipitated withdrawal as well as the number of such withdrawals will be generated by treatment arm. A listing of precipitated withdrawals will be provided.

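### The RCT suicidal-ideation table stops at baseline; the safety grouping and the adverse-event reporting periods also need correcting

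*Combined protocol and SAP*

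**What the plan says.** **Suicidal ideation.** SAP 8.2.3 (RCT) reads: "A summary table will be provided by site of answers to the question", the answers being those "collected on the Health Status (HST) eCRF at baseline". It adds a listing: "A listing of suicidal ideation will be generated that includes the date of the assessment and the response to the question above". Protocol 14.24 states: "The PHQ-9 will be assessed at baseline and at 7 and 30 days post enrollment for the RCT". Protocol Table 2 agrees, marking the Health Status form at enrollment, 7 days and 30 days. SAP 8.2 says that RCT safety results are shown by arm and overall, and the table list in SAP 16.2 titles this table as by treatment arm.

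**Grouping.** SAP 3.2.1.3 admits to the RCT safety population those who consented and received treatment, then says: "Safety analyses will be performed according to the participant's randomized treatment arm". The per-protocol set in SAP 3.2.1.2 is analysed by actual arm.

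**Adverse-event period.** Protocol 8.9.4: "The reporting period for AEs and SAEs for the RCT starts at XR-BUP administration". In protocol section 18, under the site's role in eliciting events, adverse-event "assessment will initiate with participant consent". Protocol 14.24.1 and SAP 3.2.2.5 each give a further definition, set out below.

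**The concern.** A safety table for a randomised comparison should show what happened after treatment, by treatment. A baseline table by site does neither: it describes the population before dosing. If it is the only summary of suicidal ideation, the trial collects follow-up answers on a recognised safety question and reports no comparison from them.

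The other two points concern attribution and collection. Grouping treated participants by randomised arm can place an event under a product that the participant did not receive. A reporting period anchored to an injection leaves sites without a clear rule for the arm that gets none, and an analysis window cannot recover events that were never collected.

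**Working it through.** No arithmetic in the plan needs reproducing; the check is a comparison of texts.

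**1. Ideation.**
- SAP 8.1.6 (ancillary) and SAP 8.2.3 (RCT) use the same wording for the summary. It fits the ancillary study: protocol Table 3 schedules the Health Status form at enrollment only, and the footnote to SAP Table 28 says that it is completed once.
- In the RCT the form is scheduled three times and SAP 8.2.3 summarises one, so 3 − 1 = 2 of 3 assessments have no planned summary.
- Could another table fill the gap? Protocol 8.9.4 and 14.24.1 both take suicide-risk assessments out of adverse-event reporting unless they meet the serious definition. Non-serious ideation at Day 7 or Day 30 therefore does not reach the adverse-event tables. The Mental Health Assessment form is in the SAP's eCRF list, but no summary of it is planned.
- The item looks back two weeks. A Day 7 answer therefore reaches about 14 − 7 = 7 days before enrollment, while a Day 30 answer covers roughly Day 16 (30 − 14) onward and is wholly after dosing. The two follow-up visits should be shown separately.

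**2. Grouping.** SAP 3.2.1.2 foresees participants who refuse the injection. Suppose one is randomised to XR-BUP and takes SL-BUP instead.
- Read literally, SAP 3.2.1.3 includes this person as treated and counts any events under XR-BUP.
- If treated means exposed as in SAP 6.2.1, an XR-BUP participant counts only if injected, so this person leaves the safety set.
- On neither reading are the events assigned to the product received.

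The documents give no crossover rate. As an assumption only: if a fraction c of the XR-BUP safety set was not injected, an injection-specific event rate is multiplied by (1 − c). That is 1.00 at c = 0, 0.95 at c = 5% and 0.90 at c = 10%.

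**3. Adverse-event periods.**

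| Place | Start | End |
|---|---|---|
| Protocol 8.9.4 | XR-BUP administration | Day 30 from enrollment |
| Protocol 14.24.1 | Study product administration | Day 30 from the injection |
| Protocol 18, site's role | Consent | Follow-up of reported events to 30 days past the last visit |
| SAP 3.2.2.5 | First dose, either arm | First dose + 30 days |

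Read literally, 8.9.4 gives the SL-BUP arm no start date and 14.24.1 gives it no end date. SAP 3.2.2.5 has neither gap: it sets the SL-BUP first-dose date at enrollment, provided the drug was given in the ED or prescribed for home induction.

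**The case against.** The best defence is that the SAP is sounder than its weakest paragraph. SAP 8.2 and 16.2 already require results by arm, the ideation listing is dated and not limited to baseline, and serious events reach the SAE tables. The revision history calls the RCT sections a first draft, to be finalised in version 4.0 before database lock. All of that stands. It still leaves no table of ideation after baseline, and a listing whose visits are unstated is not a comparison.

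Four stronger readings are tempting, and the documents do not support them.

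- *The RCT safety analyses miss harm after dosing.* They do not. Treatment-emergent AEs and SAEs, injection-site findings, additional medications, deaths, overdoses, hospitalizations and ED visits are all planned (SAP 7.2.5.7 and 8.2.1 to 8.2.8).
- *The adverse-event analysis window starts at XR-BUP dosing.* That is true only of the reporting period in protocol 8.9.4. The SAP window starts at first dose in both arms.
- *Grouping by randomised arm dilutes XR-BUP harm by a known amount.* No crossover rate is given, and SAP 6.2.1 leaves it open whether an uninjected XR-BUP participant enters the safety set at all. Injection-site percentages need not be diluted either: the ancillary shell for that form takes completed assessments as the denominator for participants with reactions.
- *The precipitated-withdrawal table is an error that restriction to COWS ≥ 8 would cure.* SAP 8.2.4 says: "A table summarizing the number of participants experiencing a precipitated withdrawal as well as the number of such withdrawals will be generated by treatment arm". This is descriptive, with no test planned. Observation does differ, because protocol 8.4.9 states a 2-hour stay for XR-BUP only and has SL-BUP participants with COWS 4-7 start at home. Since no matching stay is stated for SL-BUP at COWS ≥ 8, the restriction would not equalise ascertainment.

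**Conclusion.** The point holds in three parts of unequal weight.

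1. **Ideation, the main part.** As written, two of three scheduled assessments have no planned summary, and non-serious ideation after dosing is never tabulated by arm. This rests on the text alone. The by-site wording also contradicts SAP 8.2 and 16.2.
2. **Grouping.** The rule would misattribute events for anyone who received the other treatment. The size is unknown and may be near zero; the 5% and 10% values above are illustrations, not estimates.
3. **Reporting periods.** This is an inconsistency in the protocol's collection rules, not a fault in the SAP's analysis window. Whether it cost any SL-BUP events depends on how sites applied it, which the documents do not show.

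The primary efficacy conclusion is unaffected. What is at stake is how completely the comparative safety of an investigational product is reported.

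**What to change.** - **SAP 8.2.3:** replace the carried-over sentence. Tabulate the ideation item by arm and overall at baseline, Day 7 and Day 30, with the number newly endorsing it after a negative baseline answer. State that the listing covers all visits and shows the visit.
- **SAP 3.2.1.3:** analyse safety by treatment received, and define received treatment in line with SAP 6.2.1 so that a participant given the other product is counted under that product. If the randomised-arm grouping is kept, justify it and add an as-treated version.
- **Protocol 8.9.4, 14.24.1 and 18:** reconcile them into one reporting period with a start and an end that exist in both arms, consistent with the first-dose window in SAP 3.2.2.5. In the RCT adverse-event listing (SAP 8.2.1), replace the injection-based first-dose date with one that both arms have.
- **Optional presentation:** show precipitated withdrawal by COWS stratum (4-7 and ≥ 8, already a baseline category in SAP 5.2), with a note that observation differs by arm.

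The cost is SAP wording, a few table shells and one protocol clarification. The assessments are already scheduled, and version 4.0 of the SAP is the natural place for the SAP changes.

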#### **8.2.4 Precipitated Withdrawals**

A table summarizing the number of participants experiencing a precipitated withdrawal as well as the number of such withdrawals will be generated by treatment arm. A listing of precipitated withdrawals will be provided.

